#### Assessment of secondary endpoints

Salivary cortisol will be assessed, using the Salivette (manufactured by Sarstedt, Etten-Leur, The Netherlands), at 3 out of the 4 time points, corresponding to the assessment of patient-centered outcomes and psychological variables (i.e., T_0 _= 5 to 10 days after ICD implantation; T_1 _= 14 weeks post-implantation; T_3 _= 52 weeks post-implantation). Due to test-retest reliability characteristics of cortisol [34,35], samples will be taken on two consecutive weekdays at each time point. Four samples will be taken at each time point and on the consecutive day, that is (a) when waking up, (b) 1/2 hour later, (c) 11.00 a.m., and (d) 3.00 p.m. Samples will be sent to the coordinating trial center, where they will be stored at -20°Celsius until assayed.

Information on ventricular arrhythmias will be gathered from the electrograms stored by the ICD that will be reviewed and classified by two experienced electrophysiologists from the EP staff of the participating centers, who are blind to whether patients are assigned to the treatment or usual care arm. In case the two reviewers disagree about the diagnosis, a third one will be consulted to reach a consensus. For each episode, the date, type, and mean cycle length of the tachyarrhythmia will be recorded, as well as the type and outcome of delivered ICD therapy. The arrhythmia will be classified as (1) ventricular tachyarrhythmia or (2) atrial tachyarrhythmia without a coexistent ventricular arrhythmia. Therapy triggered by ventricular tachyarrhythmia will be considered as appropriate, while therapy delivered for atrial tachyarrhythmia (including atrial fibrillation, atrial flutter, atrial tachycardia, sinus tachycardia) or T wave oversensing and noise will be defined as inappropriate

### Intervention versus usual care

Patients randomized to the treatment arm will receive an internet-based intervention starting 2 weeks after implantation. They will receive a username and password to access the intervention via the web. Every week an automated email will be sent to the participants to explain the contents and exercises for the coming week. All the information, as well as the exercise forms, will be downloadable from the website in case participants prefer to read the information on paper. Master's level psychology students, trained and supervised by psychologists will provide feedback on the completed exercises. This feedback is not meant to be therapeutic; it will be directed toward mastering the problem-solving strategies. The maximum amount of time the psychology students should spend on feedback will be 60 minutes per participant. The components of the intervention are presented in Table 2. The intervention has to be completed within 12 weeks, as we learnt in an earlier trial that one session a week is too fast a pace for most people. A typical session takes about 30 minutes and consists of an introduction, a discussion of the previous lesson's homework, new theory and homework for the subsequent week. The sessions are designed to be followed on a weekly or two-weekly basis. These time indications may vary among users. Besides the sessions, the participants have several resources at their disposal: a homework station, extra information, reading tips, useful links, and addresses for additional help. Patients randomized to the usual care arm will receive care as it is standardly offered to ICD patients in the three centers, comprised of an information booklet about ICD treatment, standard clinical follow-up visits, and home monitoring of the device (if applicable).

**Table 2 T2:** Components of the 12-week web-based intervention

*Components*	*Topics dealt with*
**▪ Psycho-education about the ICD**	▪ Emotional reactions to ICD therapy
**▪ Problem-solving skills**	▪ Which aspects of ICD therapy may lead to distress
**▪ Cognitive restructuring**	▪ How to deal with shocks
	▪ Disease-specific issues and fears
**▪ Relaxation training**	▪ How to prevent the avoidance of activities
**▪ Personalized feedback by a therapist via the computer**	▪ Interpretation of bodily symptoms
	▪ How to cope with uncertainty
	▪ Help-seeking behaviour
	▪ How to cope with stress

### Statistical analysis and power calculation

The trial is designed to show whether a web-based behavioral intervention is effective in improving patient-centered outcomes compared to usual care. The power analysis was performed in relation to anxiety as the primary endpoint, since anxiety is a pertinent outcome measure in ICD patients due to the unique feature of the ICD being able to provide a shock. With (i) an expected between group effect size of .30., based on a recent meta-analysis of web-based intervention for symptoms of anxiety and depression [36] and taking into consideration that our population consists partly of patients with subclinical anxiety and depression levels; (ii) alpha = 0.05; (iii) power = 0.80 (two-sided test), 350 patients are needed (i.e., 175 in each condition). Although we had a response rate of 82% in an earlier study [16,19], based on a more conservative response rate of 50%, 700 patients need to be approached.

The effectiveness of the intervention will be examined using the intention-to-treat principle, with the inclusion of all randomized participants in the statistical analysis regardless of whether they completed the intervention or the follow-up measurements. Missing data will be imputed using regression imputation techniques. Univariable and multivariable regression analyses (both linear and Cox proportional hazard regression analysis) and analysis of variance and analysis of covariance with repeated measures will be used to investigate the effect of the intervention on the endpoints. The type of regression analysis will depend on the endpoint in question. Demographic, clinical and psychological variables will be included in multivariable analyses in order to control for their potential confounding effects. A p-value < 0.05 will be used to indicate statistical significance. All data will be analyzed using SPSS 17.0 for Windows (SPSS Inc., Chicago, Illinois).

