### Study population and eligibility criteria

Consecutive patients (N = 350) hospitalized for the implantation of an ICD in three medical centers in The Netherlands will be approached for study participation while in hospital and randomized to the intervention arm (n = 175) versus usual care (n = 175) at baseline (5-10 days post implantation). Patients (i) being implanted with an ICD, (ii) between 18-75 years of age, (iii) speaking and understanding Dutch, (iv) with access to and ability to use the internet, and (v) providing written informed consent will be eligible to participate. Patients with a life expectancy less than 1 year, with a history of psychiatric illness other than affective/anxiety disorders, on the waiting list for heart transplantation, or with insufficient knowledge of the Dutch language will be excluded.

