### Study procedure, randomization and follow-up

The study protocol will be approved by the medical ethics committees of the participating centers. The study will be conducted according to the Declaration of Helsinki, as amended in 2008 by the World Medical Association, and all patients will be informed orally and in writing about the purpose, rights, and possible benefits/risks of the study.

Patients will be invited to participate in the study while hospitalized for their ICD implantation. Patients responding positively to the invitation will be given the informed consent form and the baseline questionnaire package. In order to avoid measuring pre-operative stress, patients will be asked to complete the baseline assessment between 5 and 10 days (T_0_) after implantation. If the baseline questionnaire is not returned within 7 days, patients will receive a reminder telephone call. When the signed informed consent form and completed baseline assessments are received at the trial coordinating center, the coordinating center will randomize the patient either to the treatment arm or to usual care. There will be a separate randomization list for each participating hospital. The patient will be informed by telephone to which condition he/she has been randomized and the procedure for the rest of the study. If the patient is randomized to the internet intervention, he/she will receive a login and password in order to be able to access the intervention. The day of randomization will be the first day of the intervention period, with the duration of the intervention being 12 weeks. For both study conditions, the follow-up assessments will take place 14 (T_1_), 26 (T_2_), and 52 weeks (T_3_) post implantation. All randomized patients, irrespective of condition, will be followed until the scheduled study end. A schematic representation of the study design is shown in Figure 1.

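### Missing data are to be filled by regression imputation, with no step named that carries imputation uncertainty into the standard errors; read as single imputation, this inflates type I error or dilutes the effect

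*Protocol article*

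**What the plan says.** All of the relevant text is in the protocol article, section Statistical analysis and power calculation, unless stated.

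- Analysis set: intention to treat, "with the inclusion of all randomized participants in the statistical analysis regardless of whether they completed the intervention or the follow-up measurements".
- Missing data: "Missing data will be imputed using regression imputation techniques".
- Analysis: univariable and multivariable regression (linear or Cox), and "analysis of variance and analysis of covariance with repeated measures will be used to investigate the effect of the intervention on the endpoints".
- Decision rule: "A p-value < 0.05 will be used to indicate statistical significance".
- Schedule (section Study procedure, randomization and follow-up): "the follow-up assessments will take place 14 (T_1_), 26 (T_2_), and 52 weeks (T_3_) post implantation".

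The section does not say whether one value or several are imputed, whether arm is in the imputation model, or how imputation uncertainty reaches the p-values. It gives no dropout rate. Its 50% figure is the response expected among patients approached.

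**The concern.** This is a stated method, not a topic left open for a later analysis plan. A regression prediction is not an observation. If one prediction fills each gap and the completed file goes through ordinary ANCOVA, the software counts 350 patients' worth of information whatever number supplied data. There are two ways to build the imputation model, and each does its own damage:

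- **Arm included.** The imputed values repeat the treatment difference seen in the observed patients and lie exactly on the fitted line. The estimate is unbiased under missing completely at random, but its standard error is too small.
- **Arm omitted.** The imputed values are the same for both arms at a given baseline score, so they pull the arms together.

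The rule governs the questionnaire endpoints, including anxiety, on which the trial was sized. The damage grows with the missing fraction, and follow-up runs to 52 weeks.

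**Working it through.** **1. The plan's own figure.** The inputs are "an expected between group effect size of .30" and two-sided alpha 0.05, with "power = 0.80 (two-sided test), 350 patients are needed (i.e., 175 in each condition".

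n per arm = 2(1.960 + 0.842)² / 0.30² = 174.4, rounded up to 175, so 350 in total; power at 175 per arm is 0.801. The figure reproduces. It requires all 350 patients to supply data, so it holds no allowance for dropout.

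**2. Assumptions for the rest (not in the documents).** One normal follow-up score with SD 1; baseline-to-follow-up correlation r = 0.6, with 0.4 and 0.5 as alternatives; a fraction d = 10%, 20% or 30% missing completely at random; analysis by ANCOVA on baseline. Allocation is from the protocol: "randomized to the intervention arm (n = 175) versus usual care (n = 175".

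**3. Arm in the imputation model, by formula.** Residual SD = √(1 − 0.6²) = 0.8. With complete data, SE = 0.8 × √(2/175) = 0.0855. With a fraction d missing:

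- true SE ≈ 0.0855 / √(1 − d), since only observed patients inform the estimate;
- reported SE ≈ 0.0855 × √(1 − d), since imputed points add zero residual but count as patients;
- ratio reported/true = 1 − d, so actual alpha ≈ 2[1 − Φ(1.96(1 − d))].

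| Missing | True SE | Reported SE | Alpha, formula | Alpha, simulated r = 0.6 | Alpha, simulated r = 0.4 |
|---|---|---|---|---|---|
| 10% | 0.090 | 0.081 | 7.8% | 8.0% | 6.7% |
| 20% | 0.096 | 0.077 | 11.7% | 12.4% | 11.6% |
| 30% | 0.102 | 0.072 | 17.0% | 17.9% | 16.5% |

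The simulations used 4,000 trials per setting at r = 0.6 and 3,000 at r = 0.4. Simulated true and reported SEs at r = 0.6 were 0.089 and 0.081, 0.097 and 0.077, 0.102 and 0.071. Two further sets of runs at r = 0.5 gave about 8%, 13%, 17% and 8%, 11%, 16%. Adding one random residual to each prediction does not cure it: 7.8%, 10.9% and 14.6% at r = 0.6.

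**4. Arm omitted.** Simulated type I error is 5.5%, 5.5% and 5.0%, so there is no inflation. The expected estimate is about 0.30 × (1 − d) = 0.27, 0.24, 0.21; simulation gives 0.270, 0.239, 0.211. The reported SE (0.081, 0.077, 0.072) now matches the spread of the estimate, so the p-value is not anti-conservative, but the interval is centred in the wrong place. At 20% missing the bias is 0.239 − 0.30 = −0.061, or 0.79 SE, and a 95% interval covers 0.30 with probability about Φ(1.96 + 0.79) − Φ(−1.96 + 0.79) = 0.997 − 0.121, near 88%.

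**5. Average over T1-T3, other visits used in the imputation.** Deterministic imputation with arm, baseline and the patient's other visits in the model; equal correlations of 0.5 or 0.7; 1,500 trials per setting. With dropout building up to 10%, 20% and 30% by 52 weeks, type I error for the average effect is about 6-7%, 8% and 9-10%. With intermittent gaps at those rates per visit it is about 5%, 8% and 10-11%. A test at 52 weeks alone stays high, at about 6-7%, 11-12% and 15-17%.

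**6. A method that carries the uncertainty.** Multiple imputation (20 imputations, arm in the model, Rubin's rules), r = 0.6: type I error 5.5%, 5.3% and 5.0%, nominal within simulation error.

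**The case against.** A reader might infer that the protocol commits to single imputation and that the type I error of the trial therefore exceeds 5%. The text does not support that. It speaks of techniques in the plural, never says one value per gap, and does not rule out regression-based multiple imputation. Inflation needs a second unstated choice as well, namely arm in the imputation model; without it the test keeps its level. Both points stand, and the conclusion has to be conditional.

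It is also fair to say that a single-visit test is close to the worst case. The plan lists repeated-measures analyses, and step 5 shows clearly smaller inflation when visits are averaged and inform each other. The dropout range is assumed, not the sponsor's.

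A reader might add that patients who die would be given imputed anxiety or quality-of-life scores. The imputation sentence is silent on death, patients with a life expectancy under one year are excluded, and no number of deaths can be derived. The point does not carry this finding.

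Last, an article may leave imputation variables, number of imputations and sensitivity analyses to a fuller document, and their absence is not criticised here. What remains is that the article does name a method, and its usual meaning is one that cannot give correct standard errors and an undiluted effect together.

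**Conclusion.** The point holds in conditional form. As worded, the missing-data rule includes nothing that carries imputation uncertainty into the standard errors. Under the usual reading, the result is one of two faults:

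- Arm included: type I error of roughly 7-8%, 11-13% and 16-18% at 10%, 20% and 30% missing for a single-visit test, and about 6-10% for an effect averaged over visits.
- Arm omitted: type I error near 5%, with an effect of 0.30 reduced to about 0.27, 0.24 and 0.21.

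The figures rest on data missing completely at random, normal scores, assumed correlations and an assumed dropout range. They show the mechanism and its order of size; they do not predict this trial's error rate. If multiple imputation with proper pooling was meant, the defect is one of wording only.

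**What to change.** Replace the imputation sentence with one of two methods:

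- a likelihood-based mixed model for repeated measures on all observed T1-T3 scores, adjusted for baseline, with no imputed values; or
- multiple imputation with arm in the imputation model (or done separately by arm), combined by Rubin's rules.

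Two details of Table 1 bear on the choice. The health care utilization questionnaire is taken only at baseline and 52 weeks, so a repeated-measures model has little to work with there and multiple imputation fits better. The posttraumatic stress scale has no baseline to adjust for. If the mixed model is chosen, the intention-to-treat sentence should make clear that patients are analysed as randomized using all observed scores, since a patient with no follow-up score adds nothing to that model. If multiple imputation was the intention, it is enough to say so and name the pooling rule.

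The cost is a change of wording, a little more analysis work, and confidence intervals wider than those from single imputation. No extra patients or visits are needed.

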## Discussion

The ICD is generally well accepted by patients [8], but 25-33% of patients experience clinical levels of anxiety, depression, and impaired QoL following implantation [9-12].

Preliminary evidence suggests that psychological and behavioral intervention may mitigate the development of adjustment problems in ICD patients, but the number of large-scale intervention trials in ICD patients is scarce [25-27]. In addition, all of these trials have used a nurse-based approach, cognitive behavioral therapy as stand-alone therapy, or in combination with cardiac rehabilitation. A web-based intervention may be equally effective and have advantages over these more traditional forms [28]. The **WEB**-based distress management program for implantable **CAR**dioverter d**E**fibrillator patients (WEBCARE) is a multi-center, multi-disciplinary, randomized, controlled behavioral intervention trial designed to examine whether a web-based approach leads to better patient-centered outcomes, in terms of reduced levels of anxiety and device concerns and improved QoL. The trial aims to include 350 patients from three Dutch centers.

## Abbreviations

ICD: Implantable cardioverter defibrillator; QoL: Quality of life; SCD: Sudden cardiac death.
